**Title**

Does a sutured-on-stent dressing for incisional protection during anaesthetic recovery reduce the incidence of surgical site infection following exploratory laparotomy compared to a standard textile adhesive dressing?

**Introduction****Background and rationale:**

Surgical site infection following midline laparotomy is an important complication following laparotomy in horses with rates of 16-26.9% reported (1-4). Infection results in increased hospital stay, increased costs, delayed incisional healing and increased risk of incisional hernia formation requiring potential surgical repair. At the Philip Leverhulme Equine Hospital midline laparotomy incisions are routinely covered with a Primapore dressing followed by an adhesive sheet for recovery following anaesthesia. The dressing often comes off during recovery leaving the surgical site open to contamination. A recent retrospective study using stents to protect midline laparotomy incisions reported reduced infection rates of 2.7% compared to 21.8% without stents for recovery (4). However, this study had a number of biases and other limitations due to its retrospective nature.

**Objectives:**

To perform a randomised controlled trial to determine if use of a sutured-on-stent for anaesthetic recovery reduces the proportion of horses that develop a surgical site infection (SSI) following laparotomy compared to a standard textile adhesive dressing.

**Trial design:**

Parallel group randomised controlled trial

**Methods - Participants, Interventions and outcomes****Study setting:**

Horses undergoing exploratory laparotomy at the Philip Leverhulme Equine Hospital for treatment of colic (acute abdominal pain).

**Eligibility criteria:**

Horse undergoing exploratory laparotomy from November 2013 onwards with owner informed consent.

### Inclusion criteria

- All horses (defined as a horse, pony or donkey) > 1 year of age with owners that provide informed consent for trial inclusion
- Horses in which surgery is completed and the horse walks out of the recovery box. Recovery from general anaesthesia is defined as the horse walking out of the anaesthetic recovery box.

### Exclusion criteria

- Equine Grass Sickness confirmed histologically following ileal biopsy

### Intervention:

Horses will be randomly assigned to one of two groups for protection of the skin incision just prior to incisional closure. Incisional closure will be performed in normal fashion as per surgeon preference.

1. Stent group - a commercial stent (Kruuse) will be placed over the incision and will be secured in place using six interrupted sutures. An adhesive dressing will be applied over the stent and a textile bellyband placed as the horse is transferred to the recovery box.
2. Control group - a Primapore dressing will be applied to the incision followed by an adhesive dressing and a textile bellyband placed as the horse is transferred to the recovery box.

When the horse is moved out of the recovery box dressings in both groups will be removed and will be replaced by a sterile Melonin dressing followed by an adhesive abdominal bandage. Both groups will be managed in the same way regarding perioperative care based on standard hospital practice and based on clinician preference.

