### Allocation concealment:

A box containing sequentially numbered, opaque, sealed envelopes will be used to randomly assign cases to one of two groups. Inside each sealed envelope will be a paper sheet assigning the horse to either the Stent or Control group for method of incisional protection during anaesthetic recovery. The next envelope in the sequence will be opened once patient eligibility has been confirmed and allocation recorded.

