### Blinding:

Blinding will be performed by photographs being taken in a standard fashion at each dressing change for each horse. These will be reviewed independently during data analysis.

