#### Preoperative data

- Age (years)
- Sex (gelding, stallion, mare)
- Breed (various)
- Weight (kg)
- Date of surgery
- Day of the week of surgery (Mondays to Sunday)
- Time of induction of anaesthesia
- Month of surgery (January- December)
- Heart rate on arrival (beats per minute)
- Packed cell volume on arrival (%)

- Systemic total protein on arrival (g/L)
- Systemic lactate on arrival (mmol/L)
- Peritoneal total protein on arrival (g/L)
- Peritoneal lactate on arrival (g/L)
- Coat condition on arrival (clean clipped/clean unclipped/moderate/filthy)

Perioperative data

- Primary surgeon (various)
- Primary surgical lesion (various)
- Decompression of SI only (Y/N)
- SI resection (Y/N)
- Length of resection (feet)
- SI resection – EEJJA (Y/N)
- SI resection – EEJIA (Y/N)
- SI resection – SSJCA (Y/N)
- LC resection (Y/N)
- LC reposition (Y/N)
- LC enterotomy (Y/N)
- SC enterotomy (Y/N)
- SC resection (Y/N)
- Number of layers used to close the midline (2/3)
- Suture material for linea alba (vicryl / other)
- Suture material for subcutaneous layer (vicryl/ other/none)
- Suture material for skin (prolene/ vicryl / staples/other)
- Suture pattern for linea alba (simple continuous/ halves of simple continuous/centre cruciate followed by halves of simple continuous/ other)
- Suture pattern for subcutaneous layer (subcutaneous /other)
- Suture pattern for skin (Ford interlocking / simple continuous/ none i.e. staple)
- Duration of general anaesthesia (minutes) (defined as from time of induction to disconnection from breathing circuit)
- Duration of surgery (minutes) (defined as time from first incision to last suture placement)
- Depth of thickest adipose tissue of midline prior to closure as measured with sterile ruler (cm)
- Length of incision prior to closure as measured with sterile ruler (cm)
- Recovery dressing (primapore followed by opsite adhesive & textile abdominal bandage) or sutured sterile stent followed by opsite adhesive & textile abdominal bandage
- Recovery score following general anaesthesia as per Guelph chart (1-6)
- Was the incision covered for the duration of recovery (Y/N)

- Type antimicrobial administered prior to surgery (sodium penicillin and gentamicin/ procaine penicillin and gentamicin/ other)

*Follow up data*

- HR @24h (beats per minute)
- Temperature @24h ( C)
- PCV@24h (%)
- TP@24h (g/L)
- HR@ 48h (beats per minute)
- Temperature @48 h @ ( C)
- PCV @48h (%)
- TP @48h (g/L)
- Colic signs post operatively (Y/N)

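### The arm is revealed before closure, and closure is left to the unblinded surgeon, so closure technique could differ by arm; open the envelope after skin closure instead

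*Protocol*

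**What the plan says.** The Intervention section of the protocol sets the time of assignment: "Horses will be randomly assigned to one of two groups for protection of the skin incision just prior to incisional closure". The sentence after it reads "Incisional closure will be performed in normal fashion as per surgeon preference".

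Allocation concealment has its own rule for the envelope: "The next envelope in the sequence will be opened once patient eligibility has been confirmed and allocation recorded". It does not hold the envelope until closure is finished.

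The perioperative items under Data collection methods show how far closure may vary between horses. They include "Number of layers used to close the midline (2/3", "Suture material for skin (prolene/ vicryl / staples/other" and "Suture pattern for skin (Ford interlocking / simple continuous/ none i.e. staple", with similar lists for the linea alba and the subcutaneous layer.

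On masking, the Blinding section says "Blinding will be performed by photographs being taken in a standard fashion at each dressing change for each horse", with independent review during data analysis. The Intervention section also says that perioperative care will be the same in both groups, but makes that care depend on standard hospital practice and clinician preference.

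**The concern.** The surgeon learns the arm and then makes several choices about how to close the wound whose infection is the primary outcome. If those choices shift with the arm, the SSI comparison mixes the effect of the dressing with the effect of the closure.

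The exact term is performance bias: a co-intervention chosen after randomisation, not a baseline imbalance. Randomisation does not protect against it, and the planned baseline comparison would not be a test for it. Photograph review concerns outcome assessment and cannot undo a different closure. Recording the closure variables lets an imbalance be described. However, adjusting for a variable that the allocation may have influenced does not reliably remove the bias.

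The early reveal also looks avoidable. The arms differ in what is put over the closed incision, and the protocol gives no reason for revealing the arm before closure.

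**Working it through.** **1. Order of events**

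| Step | Source in protocol | Arm known to surgeon? |
|---|---|---|
| Assignment, shortly before closure | Intervention | becomes known |
| Closure, technique at surgeon's discretion | Intervention; perioperative data list | yes |
| Stent or Primapore put on over the incision | Intervention | yes |

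If closure is read narrowly as skin closure only, the choice of skin material and pattern still follows the reveal. No section fixes the technique, has the surgeon declare it before the envelope is opened, or stratifies by surgeon or closure method.

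**2. The plan's own figure (Sample Size section)**

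Inputs: SSI 20% v 10%, power 80%, 5% significance (two-sided assumed), 1:1 allocation.

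n per arm = (1.960 + 0.842)² × (0.20×0.80 + 0.10×0.90) / 0.10² = 7.849 × 0.25 / 0.01 = 196.2, rounded up to 197.

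The stated 197 per group reproduces. With a pooled standard error, power at 197 per arm is 79.6%.

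**3. Illustration A: bias in favour of the stent**

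These inputs are assumptions; the documents give none. Knowing the arm changes closure in a fraction f of one arm, and the alternative closure differs by 10 points in SSI risk.

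Bias = f × 10 points. So f = 20% gives 2 points and f = 30% gives 3 points.

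Rejection probability with no stent effect, n = 197 per arm, two-sided 5%:
Φ[(Δ − 1.960·SE₀)/SE₁] + Φ[(−Δ − 1.960·SE₀)/SE₁], where SE₀ = √(2p̄(1−p̄)/n) and SE₁ = √(p₁(1−p₁)/n + p₂(1−p₂)/n).

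- 20% v 18%: SE₀ = 0.0395, SE₁ = 0.0395; 0.073 + 0.007 = 8.0%.
- 20% v 17%: SE₀ = 0.0391, SE₁ = 0.0391; 0.116 + 0.003 = 11.9%.

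**4. Illustration B: a wider range, bias against the stent**

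Also assumed: a closure technique multiplies SSI risk by R and is used d more often in the stent arm, with average use 50% and control SSI 20%.

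Use is c = 0.5 − d/2 (control) and s = 0.5 + d/2 (stent). Base risk r = 0.20/(1 + c(R−1)). Stent-arm risk = r(1 + s(R−1)).

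| R | d | Stent-arm SSI, no stent effect | Bias (points) | Stent-arm SSI, true halving | Power at 197 per arm |
|---|---|---|---|---|---|
| 1.25 | 10 points | 20.4% | 0.4 | 10.2% | 77.5% |
| 1.5 | 20 points | 21.7% | 1.7 | 10.8% | 71.4% |
| 2.0 | 20 points | 22.9% | 2.9 | 11.4% | 64.8% |
| 2.0 | 30 points | 24.4% | 4.4 | 12.2% | 55.6% |

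At the top row almost nothing is lost from 79.6%. At the bottom row the loss is material. If the technique were used more in the control arm, the bias would run the other way and favour the stent.

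**The case against.** The strongest reply is that this is a design choice, not an error. Closure is to be done in the usual way, care is meant to be the same in both groups, and every closure variable is recorded. No mechanism is given by which a dressing worn only during recovery would lead a surgeon to change layers or sutures. Variation between surgeons is not variation by arm. Under intention to treat, a shift in closure caused by assignment is part of the effect of assignment.

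Much of this stands:

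- A reader might infer that surgeons will close differently by arm. The protocol shows only that nothing prevents it.
- A reader might take 8 to 12% as the trial's actual type I error. It rests on unsourced inputs, and the 10-point closure effect equals the whole difference the trial is sized for (20% − 10%). It also presumes that the target is the effect of the stent itself, apart from any change in closure. That fits the Objectives section but is not spelled out as an estimand.
- A reader might infer from the reference list that closure technique is known to affect SSI. One cited title asks whether subcutaneous sutures raise the risk of suppuration; the answer is not in the document.
- A reader might infer that duration of surgery is longer in the stent arm by construction, because it is recorded as "Duration of surgery (minutes) (defined as time from first incision to last suture placement" and the stent is sutured on. The text does not say whether stent sutures count, and duration is neither an outcome nor a named covariate.
- The plan names no closure covariate, so no flawed adjustment is planned.

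What does not stand is the claim of a safeguard. The equal-care statement itself yields to clinician preference, and the closure sentence grants explicit discretion.

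**Conclusion.** The point holds as an avoidable route for performance bias. The arm is known before a discretionary closure by an unblinded surgeon, so closure technique is a post-randomisation co-intervention that could differ by arm.

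The direction is unknown and the size cannot be derived from the documents. Under the assumptions shown it runs from near zero to about 2 to 4 percentage points. A bias of 2 to 3 points at 197 per arm would take the rejection rate under no true effect from 5% to about 8 to 12%. A bias against the stent would cost power instead.

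The case for acting rests less on these figures than on the low cost of closing the route. The change should be made, but the present text is not evidence that the comparison is biased.

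**What to change.** Amend the Intervention and Allocation concealment sections together; changing one alone would leave two rules for opening the envelope. Suggested wording for both: the next envelope in the sequence is opened only after skin closure is complete, immediately before the recovery dressing is applied, and the closure variables are recorded before it is opened.

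Surgeon discretion over closure and both interventions stay as they are. The closure variables become pre-randomisation variables, which can be compared between arms and, if wanted, adjusted for. For any horse randomised under the present text, tabulate closure by arm. This describes an imbalance but does not remove it.

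As a minor point, state that the end of surgery in the duration definition is the last skin suture or staple, so that the definition is the same in both arms.

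The cost is a short amendment to two protocol sections and the theatre instructions, and having the stent within reach at the end of closure. The sample size is unaffected.

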### Outcomes:

Primary outcome: the proportion of horses that develop a SSI.

SSI is defined as either positive culture from an incisional discharge, discharge of any purulent material or persistent serosanguinous discharge for more than 48 hours. Mild serous discharge <24 hours post operatively will be considered a normal finding. Dressing changes will be performed every 48 hours unless required to be performed sooner. At each dressing change the surgical site will be assessed by the clinical team, graded as per visual guides and if any discharge is noted a bacteriology swab will be submitted for culture and sensitivity testing.

### Participant timeline:

Data will be collected during hospitalization for all horses. Follow up after hospital discharge will be performed via a standardized questionnaire and will be performed at two points; firstly by the referring vet at suture removal and in the first 3 months postoperatively.

### Sample Size:

Retrospective data indicate that the current prevalence of post-operative SSI following exploratory laparotomy in the hospital is approximately 20%. We hypothesise that use of a sutured-on-stent will reduce the prevalence of infection by 50% or more which we consider clinically relevant. With 80% power at 5 % significance with 20% prevalence of SSI in the control group and 10% prevalence of SSI in the stent group we require 197 horses in each group i.e. 394 in total.

## **Methods – Assignment of interventions**

### Sequence generation:

A random number generator (Excel) will be used to generate a randomised allocation sequence allowing unequal group sizes (allocation ratio 1:1).

### Allocation concealment:

A box containing sequentially numbered, opaque, sealed envelopes will be used to randomly assign cases to one of two groups. Inside each sealed envelope will be a paper sheet assigning the horse to either the Stent or Control group for method of incisional protection during anaesthetic recovery. The next envelope in the sequence will be opened once patient eligibility has been confirmed and allocation recorded.

### Blinding:

Blinding will be performed by photographs being taken in a standard fashion at each dressing change for each horse. These will be reviewed independently during data analysis.

## **Methods – data collection, management and analysis**

### Data collection methods:

Data will be collected using standard hospital forms and will include the following specific data recorded for both groups.

#### Preoperative data

- Age (years)
- Sex (gelding, stallion, mare)
- Breed (various)
- Weight (kg)
- Date of surgery
- Day of the week of surgery (Mondays to Sunday)
- Time of induction of anaesthesia
- Month of surgery (January- December)
- Heart rate on arrival (beats per minute)
- Packed cell volume on arrival (%)

- Systemic total protein on arrival (g/L)
- Systemic lactate on arrival (mmol/L)
- Peritoneal total protein on arrival (g/L)
- Peritoneal lactate on arrival (g/L)
- Coat condition on arrival (clean clipped/clean unclipped/moderate/filthy)

Perioperative data

- Primary surgeon (various)
- Primary surgical lesion (various)
- Decompression of SI only (Y/N)
- SI resection (Y/N)
- Length of resection (feet)
- SI resection – EEJJA (Y/N)
- SI resection – EEJIA (Y/N)
- SI resection – SSJCA (Y/N)
- LC resection (Y/N)
- LC reposition (Y/N)
- LC enterotomy (Y/N)
- SC enterotomy (Y/N)
- SC resection (Y/N)
- Number of layers used to close the midline (2/3)
- Suture material for linea alba (vicryl / other)
- Suture material for subcutaneous layer (vicryl/ other/none)
- Suture material for skin (prolene/ vicryl / staples/other)
- Suture pattern for linea alba (simple continuous/ halves of simple continuous/centre cruciate followed by halves of simple continuous/ other)
- Suture pattern for subcutaneous layer (subcutaneous /other)
- Suture pattern for skin (Ford interlocking / simple continuous/ none i.e. staple)
- Duration of general anaesthesia (minutes) (defined as from time of induction to disconnection from breathing circuit)
- Duration of surgery (minutes) (defined as time from first incision to last suture placement)
- Depth of thickest adipose tissue of midline prior to closure as measured with sterile ruler (cm)
- Length of incision prior to closure as measured with sterile ruler (cm)
- Recovery dressing (primapore followed by opsite adhesive & textile abdominal bandage) or sutured sterile stent followed by opsite adhesive & textile abdominal bandage
- Recovery score following general anaesthesia as per Guelph chart (1-6)
- Was the incision covered for the duration of recovery (Y/N)

- Type antimicrobial administered prior to surgery (sodium penicillin and gentamicin/ procaine penicillin and gentamicin/ other)

*Follow up data*

- HR @24h (beats per minute)
- Temperature @24h ( C)
- PCV@24h (%)
- TP@24h (g/L)
- HR@ 48h (beats per minute)
- Temperature @48 h @ ( C)
- PCV @48h (%)
- TP @48h (g/L)
- Colic signs post operatively (Y/N)
- Post operative pyrexia (defined as rectal temperature of >38.5 C on at least one occasion)(Y/N)
- POI signs following surgery (Y/N) (defined as functional complication of surgery in horses where >2L reflux was gained via nasogastric intubation on 2 or more occasions)
- Lidocaine continuous rate infusion given post operatively? (Y/N)
- Peritonitis (Y/N) (defined as two or more parameter including peritoneal white blood cell of >60 x 10^9 cell/L, peritoneal neutrophil count > 70%, peritoneal total protein > 60 g/L, increased peritoneal fluid on abdominal ultrasonography)
- Type of antimicrobial treatment (penicillin only/ penicillin and gentamicin/ other)
- Duration of antimicrobial treatment (days)
- Duration of hospital stay following surgery (days)
- SSI present (defined as any purulent or persistent serosanguinous drainage for more than 48 hours or with a positive culture) (Y/N)
- Pain on palpation @ 1st dressing change (none/mild/mod/severe)
- Wound discharge @ 1st dressing change (Yes/No)
- If discharge type of discharge (serosanguinous/ purulent/ haemorrhagic/other)
- Oedema @ 2nd dressing change (none/mild/mod/severe)
- Pain on palpation @ 2nd dressing change (none/mild/mod/severe)
- Wound discharge @ 2nd dressing change (Yes/No)
- If discharge type of discharge (serosanguinous/ purulent/ haemorrhagic/other)
- Oedema @ 3rd and consecutive dressing change (none/mild/mod/severe)
- Pain on palpation @ 3rd and consecutive dressing change (none/mild/mod/severe)
- Wound discharge @ 3rd and consecutive dressing change (Yes/No)
- If discharge type of discharge (serosanguinous/ purulent/ haemorrhagic/other)
- Presence of positive culture of discharge (Y/N)

- Bacteria and sensitivity results (descriptive)
- Pattern of sensitivity (descriptive)
- Development of hernia (Y/N)
- Repeat laparotomy (Y/N)

#### *SSI reporting:*

Swabs will be submitted for general aerobic and anaerobic bacterial culture to the microbiology laboratory at Leahurst Campus. Bacterial culture will consist of direct plating onto 5% sheep blood agar (Oxoid, UK) and the plates will be incubated aerobically and anaerobically for 2-7 days. Microorganisms isolated from positive cultures will be identified using API kits (Biomerieux, France) and also with the GNID Sensititre Identification plates (TREK Diagnostic Systems, West Sussex, UK).

#### Statistical methods:

Initial analysis will include a baseline comparison of group characteristics to check the adequacy of randomisation.

Data will be analysed according to intention to treat principles (ITT). Baseline data for each group will be assessed and continuous variables reported as means and standard deviation (Normally distributed data) or as median and interquartile range (IQR) for non-Normally distributed data. Baseline categorical data will be assessed and reported as numbers and proportions. The primary outcome (days to SSI) will be analysed using time-to-event analysis. Horses will be censored at the point of death / euthanasia or at time of loss to follow up. Time to SSI for each group will be estimated using Kaplan Meier plots and a Cox proportional hazard model.

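### The protocol names two primary outcomes: the proportion of horses with SSI, on which the trial is sized, and days to SSI, the only one given an analysis

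*Protocol*

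**What the plan says.** Three parts of the protocol treat the primary outcome as binary.

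- **Objectives:** the trial is to show whether the stent "reduces the proportion of horses that develop a surgical site infection (SSI) following laparotomy compared to a standard textile adhesive dressing".
- **Outcomes:** "Primary outcome: the proportion of horses that develop a SSI". No day is attached to this definition.
- **Sample Size:** "With 80% power at 5 % significance with 20% prevalence of SSI in the control group" and 10% in the stent group, the protocol asks for 197 horses per group, 394 in total. It gives no hazard ratio, event target or allowance for losses.

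The Statistical methods section names a different variable: "The primary outcome (days to SSI) will be analysed using time-to-event analysis". It continues: "Time to SSI for each group will be estimated using Kaplan Meier plots and a Cox proportional hazard model". Horses are censored at death or euthanasia, or when lost to follow-up. No test, difference or ratio of proportions appears anywhere.

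Two further places bear on the point. Participant timeline places follow-up after discharge at two points, "firstly by the referring vet at suture removal and in the first 3 months postoperatively". The follow-up list under Data collection methods records "SSI present (defined as any purulent or persistent serosanguinous drainage for more than 48 hours or with a positive culture) (Y/N"), and lists no date of SSI onset, of death or euthanasia, or of last contact.

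**The concern.** A primary outcome should be defined once and carry one primary analysis. Here the sections that state the question and set the sample size use one variable, and the section that sets the analysis uses another. A statistical analysis plan written from this protocol would have to overrule one of them, so this is not detail that a protocol may leave for later.

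The two variables are related but not the same quantity. A Cox model returns a hazard ratio, whereas the objective asks about the proportion infected. With death censored, one minus Kaplan-Meier estimates the risk of SSI as if death did not occur. When some horses die uninfected, that is higher than the proportion that actually develop SSI.

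The practical risk is that near the significance threshold the two analyses could disagree. The Outcomes section could then be cited for one result and the Statistical methods section for the other.

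**Working it through.** **1. Which outcome was the trial sized on?**

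Inputs from Sample Size: 0.20 v 0.10, 5% significance, 80% power. The allocation section gives a 1:1 ratio. Sidedness is not stated; two-sided is assumed because it reproduces the figure.

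- Unpooled two-proportion formula: n = (1.96 + 0.8416)² × (0.20×0.80 + 0.10×0.90) / (0.10)² = 7.849 × 0.25 / 0.01 = 196.2, rounded up to **197 per group**, the stated figure.
- The pooled formula gives 199 and the arcsine formula 195, both close. The continuity-corrected (219) and one-sided (157) versions do not reproduce it.

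The trial was therefore sized for a comparison of two proportions. By the pooled formula, power at 197 per group with complete outcomes is 0.796.

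**2. What does the same contrast mean for a Cox model?**

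Assume proportional hazards and full follow-up.

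- Hazard ratio: ln(0.90) / ln(0.80) = 0.1054 / 0.2231 = **0.472**. The risk ratio is 0.10 / 0.20 = 0.50, so the two effect measures already differ.
- Expected SSIs: 197 × 0.20 + 197 × 0.10 = 39.4 + 19.7 = **59.1**.
- Events needed, Schoenfeld: 4 × 7.849 / (ln 0.472)² = 31.40 / 0.563 = 55.8, so **56**. At a mean risk of 15% that is 56 / 0.15 = 373.3, so 374 horses.
- Events needed, Freedman: 7.849 × (1.472 / 0.528)² = 61.0, so **62** when rounded up; 62 / 0.15 = 413.3, so 414 horses.
- Power at 59 events: about 0.82 (Schoenfeld) or 0.79 (Freedman).

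The planned 394 horses lie between the two requirements.

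**3. What if horses are lost?**

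The documents give no loss rate, so these are assumptions. For the binary column, the lost share is removed from both groups (complete cases, pooled formula). For the Cox column, the same share of SSI events is removed by censoring (Schoenfeld).

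| Share lost | Binary power | Cox power |
|---|---|---|
| 0% | 0.80 | 0.82 |
| 5% | 0.78 | 0.80 |
| 10% | 0.75 | 0.78 |
| 20% | 0.70 | 0.73 |

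**4. Do the sections agree on the outcome?**

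| Section | Variable | Effect measure or method | Day fixed? |
|---|---|---|---|
| Objectives | Proportion with SSI | Reduction in proportion | No |
| Outcomes | Proportion with SSI | None named | No |
| Sample Size | Prevalence, 20% v 10% | Two proportions | No |
| Statistical methods | Days to SSI | Kaplan-Meier, Cox | No |

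The conflict is between the last row and the other three. The 3-month follow-up in Participant timeline is not tied to the outcome in any of them.

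**The case against.** The best defence is that time-to-event analysis is a legitimate way to study SSI. Read at a fixed day, one minus Kaplan-Meier approximates the cumulative risk, apart from how death is handled. Under proportional hazards, both analyses test the same direction of effect. That stands, so a reader who concludes that the planned analysis cannot answer the question goes too far. What is missing is a fixed day and agreement on one named outcome.

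A reader might also infer that the Cox model cannot be run because no onset date is listed. The documents do not support this. The data list is introduced as what the forms will include, which does not make it exhaustive. Date of surgery is recorded, as is wound discharge at each dressing change, with changes about every 48 hours and photographs at each. In-hospital onset can be placed to about 48 hours in both arms alike. Only onset after discharge, known from questionnaires, is coarse. The absent dates are a gap in the listed items and no more.

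Finally, it may be said that the Statistical methods section names a single analysis, so nothing is open to choice. That narrows the risk to a later switch justified from the Outcomes section. It does not remove it, because both sections claim the words primary outcome.

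**Conclusion.** The contradiction is real and concerns the primary outcome itself, so it must be resolved. The Objectives, Outcomes and Sample Size sections define a proportion. The Statistical methods section defines days to SSI and provides no analysis of the proportion. With no fixed day and with deaths censored, the planned curves do not deliver the proportion that the objective asks for.

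A reader might infer that the trial is underpowered for its stated analysis. It is not, on the protocol's own figures: 197 per group reproduces, and about 59 expected SSIs sit between the 56 and 62 required at a hazard ratio of 0.47. This rests on proportional hazards, full follow-up and the planned 20% and 10%. Losses would lower power under either analysis, by an amount that the documents do not allow one to fix.

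**What to change.** Name one primary outcome, in the same words, in Objectives, Outcomes, Sample Size and Statistical methods.

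**Option closest to the objective and sample size.** Define the primary outcome as SSI by 90 days (3 months) after surgery, yes or no. Compare the arms by risk difference and risk ratio, each with a 95% confidence interval, and a two-sided 5% test. State how horses that die, are euthanised or are lost before day 90 are counted; a yes/no outcome without that rule is incomplete. Keep Kaplan-Meier and Cox as secondary. The sample size of 394 stands if outcomes are complete.

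**Alternative.** If days to SSI is kept as primary, rewrite Objectives, Outcomes and Sample Size to match, base the sample size on events, and handle death as a competing event.

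In either case, add to the listed data items the date the SSI criteria were first met, the date of death or euthanasia, and the date of last contact.

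The cost is wording and three date fields. The binary option also loses some power if horses are lost and only complete cases are analysed, as tabulated above, and Sample Size makes no allowance for this.

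### Censoring deaths in the Kaplan-Meier estimate makes the curves overstate the proportion of horses that develop SSI in each arm; the Cox comparison is not affected

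*Protocol*

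**What the plan says.** The Objectives section asks whether the stent "reduces the proportion of horses that develop a surgical site infection (SSI) following laparotomy compared to a standard textile adhesive dressing". The Outcomes section repeats this target: "Primary outcome: the proportion of horses that develop a SSI". The Sample Size section also works in proportions, 20% against 10%.

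The Statistical methods section turns the outcome into a time: "The primary outcome (days to SSI) will be analysed using time-to-event analysis". On death it states "Horses will be censored at the point of death / euthanasia or at time of loss to follow up", so a dead horse and a horse lost to follow-up are treated alike. The estimators are then named: "Time to SSI for each group will be estimated using Kaplan Meier plots and a Cox proportional hazard model". No method that treats death as a competing event is mentioned.

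Two other sections determine which deaths matter. Under Inclusion criteria the trial takes "Horses in which surgery is completed and the horse walks out of the recovery box", so deaths in theatre or in recovery are outside the analysis and later deaths are inside it. The Participant timeline section places follow-up after discharge at two points, "firstly by the referring vet at suture removal and in the first 3 months postoperatively".

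**The concern.** Loss to follow-up and death are different kinds of event. A horse that is lost may still develop SSI unseen, and Kaplan-Meier allows for this by giving it the later risk of the horses still observed. A dead horse has no later risk. Giving it one turns 1 minus Kaplan-Meier into the SSI risk that would apply if no horse died. That is not the proportion of horses that develop SSI, and a larger trial does not remove the gap.

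What is at stake is the absolute result: the incidence shown for each arm and any absolute difference a reader takes from the curves. These would also not be like for like with the 20% hospital prevalence in the Sample Size section or the published rates in the Introduction, if those are crude proportions, as they read.

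**Working it through.** **The plan's own figure.** With a two-sided 5% level, 80% power and unpooled variances, n per group = (1.960 + 0.842)² × (0.20 × 0.80 + 0.10 × 0.90) / 0.10² = 7.849 × 0.25 / 0.01 = 196.2, rounded up to 197. The protocol's 197 per group is reproduced. It is a comparison of two proportions, which confirms the scale on which the trial was planned.

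**Inputs.**
- F, the true proportion developing SSI: 20% control and 10% stent (Protocol, Sample Size).
- D, the proportion dying or euthanised without SSI after leaving the recovery box: not given in the protocol. Assumed here to lie between 5% and 30% and to be equal in both arms.
- Timing of deaths relative to SSI: not given. Three patterns are tried.

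**Pattern 1: constant hazards of SSI and death.** With cause-specific hazards a (SSI) and b (death) over the follow-up period, F + D = 1 − exp(−(a + b)) and F/(F + D) = a/(a + b). Hence

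1 − KM = 1 − exp(−a) = 1 − (1 − F − D)^(F/(F + D)).

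For example, at D = 10%:
- control: 1 − 0.70^(0.20/0.30) = 21.2%
- stent: 1 − 0.80^(0.10/0.20) = 10.6%

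| Deaths without SSI (assumed) | 1 − KM, control | 1 − KM, stent | Difference (points) | Ratio stent/control |
|---|---|---|---|---|
| 0% | 20.0% | 10.0% | 10.0 | 0.500 |
| 5% | 20.6% | 10.3% | 10.3 | 0.500 |
| 10% | 21.2% | 10.6% | 10.6 | 0.499 |
| 20% | 22.5% | 11.2% | 11.3 | 0.497 |
| 30% | 24.2% | 12.0% | 12.2 | 0.495 |

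The true values are those of the first row throughout.

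**Pattern 2: every death precedes every SSI.** Then 1 − KM = F/(1 − D).
- D = 10%: 0.20/0.90 = 22.2% and 0.10/0.90 = 11.1%.
- D = 30%: 0.20/0.70 = 28.6% and 0.10/0.70 = 14.3%.

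This is the unfavourable extreme.

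**Pattern 3: deaths spread evenly over 90 days, SSI arising evenly over days 2 to 14 (both assumed).** The mean day of SSI is 8, so about D × 8/90 of the SSIs are pre-empted by death. Against a Kaplan-Meier value of 20% in the control arm:
- D = 10%: overstatement about 20 × 0.10 × 8/90 = 0.2 points.
- D = 30%: overstatement about 20 × 0.30 × 8/90 = 0.5 points.

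If all deaths came after the last SSI, the overstatement would be zero.

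The direction is therefore the same whenever any horse dies free of SSI while others still go on to develop it. The size depends on how many die and when.

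**The case against.** The strongest reply is that the planned comparison is sound. Treating deaths as censored in a Cox model is the standard way to obtain a cause-specific hazard ratio, which does not require death and SSI to be independent. For a dressing meant to protect the incision, that contrast is a sensible one. The Statistical methods section plans no risk difference from the curves. With equal mortality the ratio between arms stays between 0.500 and 0.495 in the table above. All of this stands, and it limits the point to the absolute curves.

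It is also fair to say that the size cannot be settled from the protocol. Horses that do not leave the recovery box are already excluded, which removes the earliest deaths. Pattern 3 shows how small the excess becomes if the remaining deaths are spread out. An overstatement of several points needs many early deaths, which the protocol neither reports nor rules out.

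A reader might go further and infer that the treatment comparison is biased because mortality could differ between arms. The protocol does not support this. Under Intervention, dressings in both groups are replaced when the horse leaves recovery and both groups are then managed in the same way, so nothing suggests different death rates. If they did differ, the Kaplan-Meier difference could move either way. Under constant hazards it would be 21.16 − 11.21 = 9.95 points with 10% control and 20% stent deaths, and 22.54 − 10.56 = 11.98 points with the rates reversed. Cumulative incidence would itself then partly reflect the difference in deaths, which is a reason to report deaths by arm.

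Nor does this point show the sample size to be wrong. The change from a proportion in Outcomes to days to SSI in Statistical methods is a related but separate inconsistency.

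**Conclusion.** The point holds in a limited form. The censoring rule and the estimator are both stated, so this is a rule fixed badly and not a detail left for later. Together they yield a per-arm incidence above the proportion the protocol sets out to measure. Under constant hazards and true proportions of 20% and 10%, the excess is about 0.6 to 4.2 points in the control arm and 0.3 to 2.0 points in the stent arm for assumed deaths of 5% to 30%. The apparent absolute difference then grows from 10.0 to between 10.3 and 12.2 points. If all deaths came first, the excess at 30% would reach 8.6 and 4.3 points; if they followed the SSI period, it would vanish. These figures illustrate a range and do not predict the trial's result, because the death rate and its timing are assumptions.

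A reader might infer that the Cox result is invalid or that the relative benefit is exaggerated. Neither follows: the hazard ratio is valid as a cause-specific quantity, and the ratio of incidences is nearly unchanged when mortality is similar. The correction is worth making, but it does not put the main comparison in doubt.

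**What to change.** In the Statistical methods section:

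- Replace the Kaplan-Meier estimate with the Aalen-Johansen cumulative incidence of SSI in each arm. Treat death or euthanasia before SSI as a competing event, and censor only at loss to follow-up and end of follow-up.
- Report the 3-month cumulative incidence per arm and the difference with a 95% CI.
- Keep the Cox model and label its result a cause-specific hazard ratio for SSI.
- Report the number of deaths and euthanasias without SSI by arm.

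The cost is small. The date of death or euthanasia is already needed for the planned censoring, the methods are in standard software, and no change to design or recruitment is involved. Reported incidences will be slightly lower than the Kaplan-Meier values.
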